### Intervention group protocol

Our intervention model (figure 2) incorporates both phone-based interaction with the participants and access to both hospital and primary care medical records. A Master of Pharmacy or similar qualification is required for all clinical pharmacists performing the intervention. The clinical pharmacist initially contacts the participants within 7 days of their discharge from hospital. Other phone-based interviews are scheduled at 30 and 60 days after hospital discharge. Due to practical considerations, interviews may be rearranged to the nearest possible date. In brief, these conversations focus on misunderstands regarding new and ongoing treatments, adherence to medication and other potential DRPs, ranging from side effects to practical administration barriers.

**Figure 2 F2:**
[figure not shown]
The key features of the intervention, including both prescheduled phone interviews and repeated medical chart reviews. The intervention is initiated immediately after hospital discharge and goes on for 180 days. *Clinical pharmacist activity. **Interactions between clinical pharmacists and study participants.

In addition to the prescheduled interviews, the intervention includes repeated medical chart reviews performed on average every second week during a period of 180 days after the participants have been discharged from hospital. This activity is implemented in order to identify discrepancies between the lists of medications before, during and after hospitalisation, unanswered referrals between healthcare providers, deviating laboratory values and whether the participant has had any relevant contacts with the healthcare system (figure 2). Moreover, the medical chart reviews also function as an important basis for the interviews. In the event of multiple medication alterations or any documented signs or symptoms that might be drug-related, the clinical pharmacist conducts a medication review (table 1). This process includes several steps, such as medication reconciliation, evaluation of proper dosage and indication, signs of ADRs or side effects, check for interactions and special considerations due to impaired renal function. In brief, the exact types of DRPs can differ considerably between participants and range from administration issues and poor medication adherence to drug-induced electrolyte imbalance or orthostatic hypotension. Identified or suspected DRPs that are detected through the interviews or medical chart reviews but cannot be solved by direct communication with the participant or next of kin are instead communicated over phone with the primary care physician. In this dialogue, the clinical pharmacist describes the potential DRP being present and offers a recommendation on how to manage the issue. The physician is the person who ultimately decides on any changes to medication regimens, in which case the clinical pharmacist contacts the patient within a few days in order to confirm and reinforce the physician’s instructions. All clinical pharmacists involved in the trial have electronic access to the participants’ medical charts. This access includes physicians’ notes, laboratory records, current lists of medications and epicrises. The combined information from these sources provide a basis for both medical chart reviews and medication reviews. During the intervention, the clinical pharmacist continuously documents the time spent on the different activities for each participant.

### Public and patient involvement

There are no elements of public and patient involvement in the design and conduct of this trial, and we have no current plans of involving patients or the public in the dissemination of the research findings.

### Data collection and outcomes

All outcome data will be gathered from medical charts with the exception of self-report questionnaires. All collected research data will be coded and kept in locked archives. Before, during and after the trial, all forms and protocols used during the interventions and follow-ups that reveal individual personal data are stored according to the same principle. There will be no identifiable data in the dissemination of the results. In summary, outcomes will be measured at the time of discharge from hospital (baseline) and then after 30 and 180 days, respectively (table 2). The follow-ups on Medication Adherence Report Scale (MARS-5) and EuroQuol five-dimension (EQ-5D) are conducted by phone and preferably in conjunction with the intervention phone calls. Rehabilitation needs require that some enrolled participants are transferred to the geriatric department before leaving the hospital for home. If a participant is relocated to another clinical ward, the actual discharge from hospital will be considered as baseline, with the exception of self-reported adherence and quality of life, which are reported on the original ward. As a consequence, we contact all study participants by phone at 30 and 180 days after their first report regarding MARS-5 and EQ-5D, even if this date differs from the actual date on which they were discharged from hospital.

**Table 2 T2:** Scheduled data collection for primary and secondary outcomes

	Baseline	30 days	180 days

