**Patient characteristics**			
Age and sex	x		
Cohabitant and home healthcare	x		
Diagnoses	x		
No of medications	x		

Baseline data are collected from the date of hospital discharge. The data for MARS-5 and EQ-5D can be retrieved before the participants are discharged and the date on which questionnaires are completed are considered as baseline regarding these two outcomes.

EQ-5D, EuroQuol five-dimension; MARS-5, Medication Adherence Report Scale.

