### Limitations and risk of bias

The first and second author of this protocol are involved in the trial both as researchers and as clinical pharmacists conducting the intervention. As previously mentioned, we will undertake several measures to reduce the risk of bias that could emerge from these multiple roles. For example, we will consult external staff for the primary outcome assessment and statistical analyses. Other clinical outcomes in terms of all-cause readmissions, emergency department visits and mortality are electronically documented data with no room for subjectivity. Therefore, this risk of bias mainly applies to MARS-5 and EQ-5D, which should be considered in the interpretation of our findings. Moreover, all interviews within the qualitative part of the study will be conducted by another person than the clinical pharmacist who performed the interventions on those specific participants. Due to the nature of the intervention, neither participants nor clinical pharmacists are blinded. We do not consider the lack of blinding to be a major issue for the study, but bias related to special attention and the knowledge of being observed could possibly affect self-reported adherence and quality of life among the participants.

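### At day 30 the plan prefers to collect MARS-5 and EQ-5D alongside a counselling call that only the intervention arm receives, and that call's timing cannot always match the questionnaire clock

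*Protocol article*

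**What the plan says.** Data collection and outcomes states that the MARS-5 and EQ-5D follow-ups "are conducted by phone and preferably in conjunction with the intervention phone calls". The same section sets their timing for both arms: "we contact all study participants by phone at 30 and 180 days after their first report regarding MARS-5 and EQ-5D", and this applies "even if this date differs from the actual date on which they were discharged from hospital". The footnote to Table 2 agrees: "the date on which questionnaires are completed are considered as baseline regarding these two outcomes". The section explains why the dates can differ. Some participants move to the geriatric department before going home, but their questionnaires are completed on the original ward.

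The intervention calls are described under Intervention group protocol and are timed from discharge: "The clinical pharmacist initially contacts the participants within 7 days of their discharge from hospital", and "Other phone-based interviews are scheduled at 30 and 60 days after hospital discharge". They can shift, since "interviews may be rearranged to the nearest possible date". Adherence is among the listed topics. Current trial status describes the control contact as phone-based follow-up.

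Limitations and risk of bias accepts that bias from the researchers' double role as intervening pharmacists falls mainly on MARS-5 and EQ-5D, and that attention and being observed could affect both. It offers caution in interpretation. A separate-interviewer safeguard is given elsewhere: "all interviews within the qualitative part of the study will be conducted by another person than the clinical pharmacist who performed the interventions".

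**The concern.** Adherence and quality of life are declared secondary objectives, and both are self-reported by participants who know their treatment after the first call. The preferred procedure has intervention participants rate their adherence in or next to a pharmacist call about adherence. Controls rate theirs without such a conversation. A more favourable answer in the intervention arm could then reflect the setting of the question, and the analysis could not separate this from a true effect.

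The timing problem is separate. A call set by the discharge date and a questionnaire set by the first-report date coincide only when the two dates are close. The document does not say which rule gives way when they are not.

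**Working it through.** The plan states no figure for MARS-5 or EQ-5D that could be reproduced. The sample size of 700 concerns the primary outcome and has no bearing here.

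**Step 1: the 30-day contact in each arm.**

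| | Intervention | Control |
|---|---|---|
| Mode | Phone | Phone |
| Preferred setting of the questionnaires | Joined to the intervention call | Follow-up call only |
| Adherence discussed in that call | Yes | No intervention conversation planned |
| Order of questionnaire and counselling | Not stated in the article | Not applicable |

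The mode is the same. The purpose and content of the call differ by arm, and this follows from the stated preference itself. The document contains nothing from which the size of the resulting bias could be calculated.

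**Step 2: timing at day 30.** Let g be the number of days from first report to hospital discharge. Inputs: questionnaire at 30 days after first report (Data collection and outcomes); intervention call at 30 days after discharge (Intervention group protocol).

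- If the first-report clock prevails, both arms answer at day 30 after first report. The gap between arms is 30 − 30 = 0 days, and the answer falls 30 − g days after discharge.
- If combining the calls prevails, intervention participants answer at 30 + g days after first report and controls at 30. The gap is (30 + g) − 30 = g days.

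The document does not give g, so the values below are assumptions.

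| Assumed g (days) | Clock prevails: days after discharge, both arms | Combining prevails: days after first report, intervention arm | Gap between arms (days) |
|---|---|---|---|
| 0 | 30 | 30 | 0 |
| 7 | 23 | 37 | 7 |
| 14 | 16 | 44 | 14 |
| 21 | 9 | 51 | 21 |

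These are gaps for a participant with that g. Averaged over an arm, the gap would be the mean of g, which participants who go straight home soon after answering pull towards zero. The share transferred is not given.

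Under the common clock, a long g has another effect. The first intervention call may come as late as day 7 after discharge, so if 30 − g < 7, that is g > 23, the questionnaire can precede any intervention call. This applies to the schedule in both arms, so it dilutes the contrast and does not favour either arm.

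**Step 3: day 180.** The prescheduled intervention calls fall within 7 days of discharge and at 30 and 60 days. None falls at 180 days, so there is no call to join and the mechanism does not act there directly. One indirect route exists: the section on discontinuations applies last observation carried forward to outcomes other than time to event, so a missing 180-day score could take the 30-day value. Follow-up had been discontinued for 44 of 161 randomised participants (44/161 = 27%), but how many of them had a 30-day score is not reported.

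**The case against.** The strongest reply concerns timing. A reader might infer that the plan measures the two arms at different times. It does not: one first-report schedule is set for all participants, the case of a later discharge is foreseen, and Table 2's footnote repeats the rule. Combining calls is only a preference and can be read as giving way when dates do not match. Questionnaires are completed before randomisation and transfer follows rehabilitation need, so g should be balanced between arms. This stands. A gap between arms arises only if staff put combining the calls ahead of the common clock.

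A reader might also infer that all follow-ups are affected, or that the treating pharmacist always collects the scores. The first fails because no call is prescheduled at day 180. On the second, the article names no caller for the questionnaires. A pharmacist as caller follows only where the calls are actually joined, and a full protocol could specify more.

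Finally, the limitations section discloses bias on exactly these outcomes, and observation effects may act on controls too, since they are also phoned. That is fair, but the disclosure does not mention the joined calls, and a caution in interpretation does not remove a difference that the preferred procedure creates.

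**Conclusion.** The point holds for the 30-day contact. The stated preference joins self-report questionnaires to an adherence-focused call that exists in one arm only, which adds a response bias specific to that arm to two secondary comparisons. Its size cannot be derived from the document, so no claim is made that it is large.

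The two timing rules also need reconciling for participants whose first report precedes discharge. The scheduled gap between arms is 0 days. It becomes g days only if combining the calls prevails, and the 0 to 21 days shown rests on an assumed range for g. The document does not support the stronger statement that the arms are scheduled at different times.

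The primary outcome is unaffected: it comes from medical charts and is classified by blinded assessors. The point merits correction because the change is small and 700 − 161 = 539 participants (77%) were still to be randomised at the reported status.

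**What to change.** 1. In both arms, administer MARS-5 and EQ-5D from the same script. Where the questionnaires share a call with the intervention, complete them before any intervention conversation.
2. Where existing staffing allows, have the questions asked by a pharmacist who is not treating that participant, as is already planned for the qualitative interviews.
3. State that the common first-report clock prevails over combining calls, in both arms.
4. Record the actual questionnaire and discharge dates, so that g and any departure from the clock can be reported by arm.

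The cost is a change of protocol wording and an occasional separate short call in the intervention arm when the dates do not match. A different caller would add further calls in a population where unanswered calls already account for 9 of the 44 discontinuations, which is why item 2 is conditional. Some bias will remain, because participants are unblinded and will already have had the first counselling call in most cases. Keeping the first-report clock also leaves the dilution for participants with a long g; moving to a discharge clock would instead make the interval from baseline vary, so that change is not requested.

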**Clinical outcomes**			
Drug-related readmissions		x	x
All-cause readmissions		x	x
Emergency department visits		x	x
Mortality		x	x
**Adherence**			
MARS-5	x	x	x
**Quality of life**			
EQ-5D	x	x	x
**Patient characteristics**			
Age and sex	x		
Cohabitant and home healthcare	x		
Diagnoses	x		
No of medications	x		

Baseline data are collected from the date of hospital discharge. The data for MARS-5 and EQ-5D can be retrieved before the participants are discharged and the date on which questionnaires are completed are considered as baseline regarding these two outcomes.

EQ-5D, EuroQuol five-dimension; MARS-5, Medication Adherence Report Scale.

#### Hospital readmissions

The primary outcome is time until unplanned drug-related readmission within 180 days of being discharged from the hospital. As a secondary outcome, we also study these events within a narrower time frame of 30 days. The cause of each readmission will be retrospectively determined by a group of blinded physicians and pharmacists who are not otherwise involved in the study. This assessment group will reach a consensus decision regarding the causality of each readmission according to criteria from WHO, a method that has been used previously in similar studies.^25 34 35^ Readmissions classified as certain, probable or possible in this assessment will be regarded as drug related in the following statistical analysis. We also measure time until unplanned hospital visit (all-cause readmissions and emergency department visits), time until death, as well as frequencies of unplanned drug-related hospital readmissions and unplanned hospital visits.

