### Discontinuations and deviations from the protocol

An enrolled study participant can at any time withdraw consent to participate in the study or simply request that remaining phone calls be cancelled. Furthermore, the intervention can be discontinued for a number of other reasons, such as a change of living circumstances from home to residential care or repeated unanswered phonecalls. Importantly, we do not continue to record any new information from participants who withdraw their consent to participate in the study. Any documented death or withdrawn consent is censored in the survival analysis from that point and onwards. In all other cases of discontinued interventions, we collect data regarding hospital readmissions and emergency department visits for the complete 180-day period. Outcomes will primarily be analysed according to an intention-to-treat principle that includes all randomised participants for the time they were under observation. For outcomes other than time to event, we will apply the last observation carried forward in cases of missing data. Finally, there will be a supplementary per-protocol analysis of drug-related readmissions and questionnaires among participants who have received all prescheduled interviews during the follow-up period.

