### Statistics

For a relative risk reduction of 40% in drug-related hospital readmissions from 19% to 11%, a total study population of 700 individuals is required to achieve a statistical power of 80% at our prespecified significance level of 0.05 for two-sided tests. The estimated incidence of drug-related readmissions was observed in a previous trial within the same community, although that study was limited to elderly people with major NCD.^25^

We will present time-to-event data in Kaplan-Meier survival curves and analyse differences in survival data between the groups through log rank tests and Cox proportional hazard models. Further investigations of subgroup effects and adjustments of the regression models will be based on heart failure and cognitive impairment as prognostic factors. We will analyse secondary outcomes using various appropriate statistical tests, such as X^2^ and independent sample t-test, depending on the type of variable.

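### The last-observation-carried-forward rule, as written, covers the readmission and visit counts and adds zero events for time after death or withdrawal; these secondary outcomes should be analysed as rates over days at risk

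*Protocol article*

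**What the plan says.** The section on hospital readmissions defines several time-to-event outcomes and then adds a different kind of secondary outcome: "frequencies of unplanned drug-related hospital readmissions and unplanned hospital visits". These are counts.

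The section on discontinuations and deviations contains four statements that bear on them:

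- The missing-data rule: "For outcomes other than time to event, we will apply the last observation carried forward in cases of missing data". Counts are not exempted.
- After consent is withdrawn, "we do not continue to record any new information from participants who withdraw their consent to participate in the study".
- Censoring is stated for one type of analysis only: "Any documented death or withdrawn consent is censored in the survival analysis from that point and onwards".
- For all other discontinuations, "we collect data regarding hospital readmissions and emergency department visits for the complete 180-day period".

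The same section sets out an intention-to-treat analysis in which each randomised participant contributes the time actually observed.

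The Statistics section says that secondary outcomes will be analysed with appropriate tests, "such as X^2^ and independent sample t-test, depending on the type of variable". It assigns no particular test to the frequencies.

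**The concern.** A count of admissions or visits depends on how long the person was observed and able to have one. Carrying a cumulative count forward from the day of exit is the same as recording no further events to day 180. A participant who withdraws on day 20 without a visit is scored as zero visits over 180 days and weighs as much as someone observed throughout. Neither a chi-square test nor a t-test corrects for this, because neither uses days at risk.

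Two things follow. The frequencies are understated in both arms. If exit differs between arms, the comparison also shifts, and when exit is unrelated to risk the arm that loses more person-time looks better. Unequal exit is plausible here: only the intervention arm receives the pharmacist's interviews, participants are considered blinded only until the first call, and mortality is itself an outcome that the intervention might change.

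The rule also sits badly with the article's own intention-to-treat statement, which points to observed time.

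**Working it through.** The plan gives no figure on this point. Its sample size supplies the 19% and 11% used below. With 19% against the exact 40% reduction (0.6 × 19% = 11.4%), two-sided 0.05, 80% power and pooled variance, the standard two-proportion formula gives 350 per arm, so the stated total of 700 reproduces. Nothing below depends on that total.

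**Inputs from the article**
- Randomised by November 2019: 161. Withdrawn consent: 13. Deaths listed as a reason for discontinuation: 5 (Current trial status).
- Follow-up period: 180 days. Drug-related readmission: 19% and 11% (Statistics).

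**Assumptions**
- Exits are spread evenly over 180 days and are unrelated to event risk.
- The event rate is constant within each arm.
- Exit shares by arm are assumed, because the article reports none.

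**Step 1: share affected.** (13 + 5)/161 = 18/161 = 11.2%. Withdrawal alone is 13/161 = 8.1%. Many of the 161 had not completed 180 days, so the final share may be higher.

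**Step 2: exposure.** If a share q leaves evenly over the period, mean exposure is 1 − q/2 of full follow-up. At q = 0.112 this is 0.944. A frozen mean count is therefore about 5.6% too low.

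**Step 3: proportion with at least one event.** With cumulative hazard H = −ln(1 − p), the frozen proportion is (1 − q)·p + q·(1 − p/H).
- p = 0.19, H = 0.2107: 0.888 × 0.19 + 0.112 × 0.0983 = 0.180, instead of 0.190.
- p = 0.11, H = 0.1165: 0.888 × 0.11 + 0.112 × 0.0561 = 0.104, instead of 0.110.
- Ratio: 0.104/0.180 = 0.58, against 0.110/0.190 = 0.58. Equal exit lowers both proportions by about 5% and leaves the ratio unchanged.

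**Step 4: unequal exit, no true effect.** With 15% in one arm and 5% in the other, exposure is 1 − 0.075 = 0.925 and 1 − 0.025 = 0.975.
- Ratio of frozen mean counts: 0.925/0.975 = 0.949.
- Arms reversed: 0.975/0.925 = 1.054.
- The same 10-point gap centred on the observed share (16.2% against 6.2%): 0.919/0.969 = 0.948.

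**Step 5: the alternative.** Events divided by days at risk give (0.925λ/0.925)/(0.975λ/0.975) = 1.00 in the same null case.

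**The case against.** The strongest reply has four parts.

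**The tests are only examples.** The article does not commit the frequencies to a chi-square or t-test, and a rate model is not excluded. A separate analysis plan could name one. This stands for the choice of test. It does not remove the LOCF rule, which is stated without qualification: an analysis plan that follows it inherits the problem, and one that departs from it contradicts the protocol.

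**The scope is narrow.** Transfers to nursing homes, unanswered calls and cancelled calls do not end the collection of readmissions and emergency visits. Only withdrawal of consent and death do. This stands, so the 44 discontinuations reported must not be read as 44 truncated records.

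**Death is arguably not missing data.** The count up to death is complete, so the LOCF sentence need not apply. This stands in part. The firm case for LOCF is then withdrawal (8.1% so far; exposure 1 − 0.081/2 = 0.960). A raw count still ignores the days lost to death, and the article does not say how death is handled for the frequencies.

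**The shift is small and the imbalance is assumed.** No losses by arm are given. For drug-related readmissions, 350 × 0.2107 = 73.7 expected events per arm give a Poisson standard error of the log rate ratio of √(2/73.7) = 0.165. The shift of |ln 0.949| = 0.052 is about 0.3 standard errors. This also stands. Counts of all unplanned visits should be higher, which would make the same relative shift larger against its standard error, but the article gives no rate from which to calculate it.

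**Conclusion.** The point holds for the secondary frequency outcomes. A stated rule turns unobserved time after exit into event-free time, in tension with the article's principle of analysing observed time. On current figures both frequencies would be about 5% too low. Distortion of the comparison is conditional: it needs unequal exit or exit related to risk. A 10-point gap, which is an assumption, moves a null ratio to about 0.95 or 1.05.

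A reader might infer more than this, and the documents do not support it:

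- *That repeat admissions inflate the type I error.* This would require testing total events as if they were independent, which the article nowhere proposes. A chi-square on persons with and without an event has one observation per person, and a t-test on per-person counts uses the observed variance between persons.
- *That early leavers are counted as event-free.* Events before exit still count. Only the time after exit is set to zero.
- *That the main result is at risk.* The primary outcome and the other time-to-event outcomes do not fall under LOCF and have their own censoring rule, so this point does not touch them.

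The change should be made, but the trial's primary conclusion does not depend on it.

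**What to change.** Exempt the readmission and visit counts from LOCF. Define days at risk for each participant as the time from discharge to day 180, death or withdrawal of consent, whichever comes first, and analyse both frequencies as rates over that time. Suitable choices are a negative binomial model with log days at risk as offset, or a recurrent-event model with robust variance. Adjust for the randomisation stratum (the cognitive scale result) and report the rate ratio with its 95% confidence interval. Treat death explicitly as a terminal event: say whether the rate is meant as one while alive, and show deaths by arm beside it.

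The cost is a few sentences in the protocol or analysis plan, best settled before any unblinded analysis. No new data are needed, because dates of death and withdrawal are already required for censoring in the survival analysis. There is a small downside: the offset assumes that withdrawal is uninformative about the event rate given the covariates, so withdrawals should be reported by arm and with their timing.
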